# Atorvastatin for reduction of 28-day mortality in hospitalized COVID-19 patients: study protocol for a randomized, double-blinded, placebo-controlled, clinical trial

**DOI:** 10.1186/s13063-022-06619-9

**Published:** 2022-08-08

**Keywords:** COVID-19, SARS-CoV-2, Coronavirus, Statins, Hmg coa, Atorvastatin, Mortality, Randomized controlled trial

## Abstract

**Background:**

Although mass vaccination has reduced the severity of COVID-19, mortality is still high among hospitalized patients. Being a sepsis-like disease, an anti-inflammatory drug as atorvastatin would reduce mortality and severity in COVID-19.

**Methods:**

We designed a randomized clinical trial that recruited 220 COVID-19 patients admitted in the COVID-19 isolation hospital at Mansoura University, Egypt. One hundred ten cases were assigned to receive 40 mg atorvastatin once daily for 28 days, and 110 were assigned to receive placebo. Delta Pharm company supported the study with the drug and the placebo, which mimics the drug as regards the drug package, the tablet color, consistency, and size. All patients received the standard treatment as per the hospital protocol. The Institutional Review Board approval and the informed consent from all participants were obtained.

The primary outcome is the 28-day all-cause mortality. Additionally, we will collect the in-hospital mortality, the need for mechanical ventilation, time to clinical improvement, in-hospital thrombo-embolic events, acute kidney injury, and the hospital and the intensive care duration of stay. We plan to follow the patients up for 6 months for reporting mortality and long-term neurological, psychological, and respiratory consequences.

We will report the un-adjusted 28-mortality using *χ*^*2*^. Then, we will report the adjusted odds ratio with a pre-planned multiple logistic regression model. We will report our results using the point estimate and the 95% confidence interval and the *P*-value.

**Discussion:**

The additional issue that we would like to discuss is the added workload on the clinicians and the allied healthcare workers who performed research at the time of the pandemic. Therefore, doing research at the pandemic era was, indeed, challenging.

**Trial registration:**

The study was registered at the Clinical Trial Registry (NCT04952350) on July 1st, 2021.

**Supplementary Information:**

The online version contains supplementary material available at 10.1186/s13063-022-06619-9.

## Administrative information

Note: the numbers in curly brackets in this protocol refer to SPIRIT checklist item numbers. The order of the items has been modified to group similar items (see http://www.equator-network.org/reporting-guidelines/spirit-2013-statement-defining-standard-protocol-items-for-clinical-trials/).

## Introduction

### Background and rationale {6a}

COVID-19 has been a major global health problem. Despite mass vaccination, waves of epidemics are still striking. SARS-CoV-2 has infected more than 265 million cases all over the world. By December 5, 2021, COVID-19 caused more than 5.2 million deaths worldwide and approximately 20,919 deaths in Egypt [1]. COVID-19 increases the risk of pneumonia, cardiovascular, and thromboembolic events [2].

COVID-19 implies an aggressive immune reaction—the cytokine storm [3]. Elevated cytokines—as interleukin-6 (IL-6)—activate the nuclear factor kappa B (NF-κB) pathway, which causes sepsis, capillary damage, acute pulmonary injury, severe acute respiratory distress (ARDS), multi-organ damage, and death [3, 4]. COVID-19 survivors suffered the post-COVID syndrome, which includes pulmonary, cardiovascular, renal, and neuropsychiatric consequences. These long-term effects may result from a direct viral infection, systemic inflammation, neuroinflammation, microvascular thrombosis, and neurodegeneration [5].

β-Hydroxy β-methyl glutaryl-CoA (HMG-CoA) drugs—statins—are lipid-lowering drugs with pleiotropic effects. Statins might benefit COVID-19 patients due to their anti-inflammatory and antioxidant effects: (1) bind to the SARS-CoV-2 main protease and prevent invasion of the host cells [6]; (2) activate autophagy and regulate SARS-CoV-2 virus degradation or replication, which may reduce viral load; (3) modulate the immune response by blocking the NF-κB pathway and NLRP3 inflammasomes, so theoretically decrease the cytokine storm in COVID-19 [6]; and (4) improve the endothelial function, which participates in the pathogenesis of the COVID-19 [7].

Statins propose antithrombotic and anticoagulant effects. In a chemical-induced venous thrombosis in a murine model, atorvastatin enhanced the vein thrombus resolution [8]. In addition, using statins was associated with a lower risk of recurrent pulmonary embolism (PE) by 50 % [7].

In influenza pneumonia, studies suggest the survival benefits of statins. One study found that statins were associated with a 0.59 reduction in the odds of death before or during hospitalization [9]. Another study found a hazard ratio of death of 0.41 with a matched sample [10]. Besides, simvastatin significantly improved the 28-day survival in hyperinflammatory ARDS [11]. Speaking of COVID, statins reduced mortality by almost half with an adjusted hazard ratio (HR) of 0.58 or slowed the progression of death [12, 13].

As regards the potential neuroprotective effects of statins, they reduced the risk of Alzheimer’s disease and related dementia with HR 0.54 (0.32–0.91) and 2.45 (0.69–8.68) compared to non-statin users [14]. Statins also have neuroprotective benefits by regulating cholesterol metabolism in the brain [15].

Consequently, we designed a randomized clinical trial to investigate the role of atorvastatin in hospitalized (severe and critical cases) COVID-19 patients on the 28-day mortality and the 6-month long-term consequences. We hypothesized that atorvastatin 40 mg once daily for 28 days would reduce the 28-day all-cause mortality in adult hospitalized COVID-19 patients.

## Objectives {7}

### The study hypothesis

Atorvastatin 40 mg per day for 28 days would reduce the 28-day all-cause mortality in adult hospitalized (severe and critical) COVID-19 patients.

### The objective of the study

The objective of the study is to test the efficacy of atorvastatin 40 mg per day in reducing 28-day mortality and the 6-month consequences in hospitalized patients with severe and critical COVID19.

## Methods: participants, interventions, and outcomes {8}

We wrote the protocol according to the recommendations of the Standard Protocol Items for clinical Trials (SPIRIT 2013) guidelines [16].

The study design is as follows: double-blind randomized (1:1) placebo-controlled superiority trial.

### Study setting {9}

The study setting is as follows: Mansoura University COVID-19 Isolation Hospital, Mansoura city, Egypt

### Eligibility criteria {10}

#### Inclusion criteria

We included adult patients (≥18 years old) with severe or critical COVID-19 admitted to the COVID-19 Mansoura University Isolation Hospital. We included patients who are PCR-confirmed, clinically or radiologically diagnosed with COVID-19.

Cases are defined as severe or critical according to the WHO definition [17], where severe cases have the clinical signs of severe pneumonia and SpO_2_ < 90% on room air or RR > 30 breaths/min without any critical criteria, while critical cases have ARDS, or sepsis, septic shock or pulmonary embolism, acute coronary syndrome, or acute stroke.

#### Exclusion criteria

Exclusion criteria were chronic statin use, serum creatine kinase (CK) > 5 times the upper limit of normal (ULN), serum transaminases > 5 times ULN, acute hepatic failure, chronic liver disease (Child-Pugh Classification C), history of rhabdomyolysis or myopathies, severe renal impairment not receiving renal replacement therapy (estimated Cr cl< 30 ml/min ), pregnant and lactating women, patients who are expected to die within 48 h, or patients on chronic colchicine, cyclosporine, or ritonavir.

### Who will take informed consent? {26a}

We secured written informed consent from the patient or the legal representative if the patient was unable to give consent. The IRB of Mansoura University – Faculty of Medicine approved the protocol (Supplement S1).

One of the investigators conducted the consent process with the patient or the legal representative by signing two copies (one for the investigator and one for the patient). The consent was signed and dated by the conducting investigator and the consent provider.

Patients or their legal representatives were informed clearly that all patients have the same chances to receive the active treatment or the placebo.

We provided the informed consent form as a supplement to this protocol (Supplement S2).

### Additional consent provisions for collection and use of participant data and biological specimens {26b}

The patient consent discussed the patients’ publication of their anonymous data. The biological specimens were handled according to the institution’s protocol (Supplement S2).

### Interventions {6b}

#### Placebo

Patients in the placebo group received the standard treatment protocol according to the local guidelines. The placebo resembles the original drug regards the drug package, the tablet color, consistency, and size.

Atorvastatin has not proved its efficacy yet, so there is no harm in not receiving atorvastatin in COVID19 patients, according to the Declaration of Helsinki 2008, paragraph 32 [18].

#### Intervention {11a}

Patients were randomized to receive either placebo or enteral atorvastatin 40 mg/day for 28 days.

### Administration in unconscious or ventilated patients

The patients received the drug through a nasogastric tube.

### Criteria for discontinuing or modifying allocated interventions {11b}

The safety assessment included daily monitoring for adverse events; we checked CK level if the patient developed myalgia or unexplained weakness and stopped if CK > 10 times ULN, drug-induced hepatitis, or serum transaminases > 8 times ULN. Patients who received azole antifungals had a lower threshold for monitoring of liver injury and rhabdomyolysis.

### Strategies to improve adherence to interventions {11c}

Patients started the drug during hospitalization, and, on discharge, they received the estimated amount of their study drug and were educated to complete the 28-day treatment. Additionally, we contacted them by telephone (or WhatsApp) after their discharge to ensure adherence to treatment.

### Relevant concomitant care permitted or prohibited during the trial {11d}

All patients received the standard of care according to local hospital protocol. Antiviral treatment was allowed and recorded.

### Provisions for post-trial care {30}

We will conduct a 6-month follow-up via telephone and at the outpatient clinic. An interview with all participants will be face-to-face by trained physicians and asked to complete a series of questionnaires, including a self-reported symptom questionnaire. We will report a detailed 6-months follow-up data later.

### Outcomes {12}

#### Primary outcome

All-cause mortality will be recorded within 28 days after randomization. We will ascertain mortality by a telephone call or the national death index.

#### Secondary outcomes

A)
*Early outcomes*
Need for invasive mechanical ventilationInvasive mechanical ventilation and oxygen support duration (days)Time to clinical improvement (defined as 2-point reduction in the WHO disease ordinal progression scale [19] or discharge, whatever happens first)Serious adverse effect leading to drug discontinuationICU and hospitalization length of stay (days)CRP on days 3,7, 14, and 28SOFA score on days 3, 7, 14, and 28COVID19 WHO disease progression scale on days 3, 7, 14, and 28Incidence of acute kidney injury (AKI), defined as an increase in Scr by ≥ 0.3 mg/dl in 48 h or increase in Scr by ≥ 50% in 7 days or oliguria for ≥ 6 h [20]In-hospital deep vein thrombosis or PEMortality at hospital discharge

CRP, D-dimers, SOFA scores, WHO disease progression score, and AKI were evaluated only during the hospitalization period.B)*Late outcomes*: (will be published in a separate report)6-month all-cause mortalityLong-term outcomes of 6 months post-acute COVID19 syndrome▪ Pulmonary function tests (PFTs), high-resolution computed tomography of the chest, and incidence of cognitive impairment.▪ Health-related quality of life (anxiety or depression) and re-hospitalization rates▪ Extrapulmonary organ function (including eGFR, and ultrasonographic features of kidney, and liver)

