### Sample size {14}

A sample size of 97 patients in each group would achieve at least 80 % power to detect a risk difference of 0.2 (20%) in the 28-day all-cause mortality (primary outcome) between the null hypothesis (both proportions are 0.6) and the alternative hypothesis (the proportion in the non-statin group would be 0.4).

Based on two large studies on chronic use of statin in hospitalized COVID patients, the adjusted OR of mortality was 0.52 and 0.67, which corresponds to a risk reduction of 17–27 % in mortality when the mortality is 60% in the control group; therefore, we used the 20% reduction in our assumption of the sample size [21, 22].

We assumed a significance level (*α*) of 0.05 and used the chi-square test of independent proportions in MedCalc software.

To compensate for the estimated loss-to-follow-up, we increased the sample size to be 110 patients in each group.

The mortality in the control group (60%) was estimated from the average mortality in January, February, and March 2021 at the Mansoura University Isolation Hospital among all hospitalized patients.

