#### Methods in analysis to handle protocol non-adherence and any statistical methods to handle missing data {20c}

We are planning to perform an intention-to-treat analysis, and we will manage missed data by analyzing the available data or by multiple imputations—reporting the method used.

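### WHO scale, SOFA and CRP at fixed days are measured only in hospital, so later comparisons (chiefly days 14 and 28) rest on survivors still admitted, a group shaped by treatment

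*Protocol article*

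**What the plan says.** The Secondary outcomes section lists CRP, the SOFA score and the WHO disease progression scale, each on days 3, 7, 14 and 28. It then limits when they were measured: "CRP, D-dimers, SOFA scores, WHO disease progression score, and AKI were evaluated only during the hospitalization period". (D-dimers appear in that sentence but not in the outcome list.)

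The section on non-adherence and missing data {20c} announces an intention-to-treat analysis and gives one rule for absent values: "we will manage missed data by analyzing the available data or by multiple imputations", with the method used to be reported.

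No section gives a patient who has died or gone home a value on these scales, or restricts the comparison to a defined population. Discharge does count in one related outcome: time to clinical improvement treats it as an improvement event.

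The Sample size section supplies the planned mortality: "The mortality in the control group (60%) was estimated from the average mortality in January, February, and March 2021", with a planned absolute difference of 0.2. The sections on adherence {11c} and retention {18b} show that some patients are expected to go home before day 28 and to be contacted by telephone.

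**The concern.** A fixed-day value requires the patient to be alive and in hospital on that day. Both conditions are settled after randomisation, and the trial expects the drug to change at least one of them. The patients with a day-14 or day-28 score are therefore not the randomised groups.

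The two permitted methods do not repair this. Analysing available data compares the remaining inpatients. Multiple imputation would create SOFA, CRP or inpatient scores for patients who have died, for whom no such value exists. For discharged patients it would extrapolate largely from people still ill enough to be admitted.

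The bias has a predictable direction. If the drug keeps some very ill patients alive, they stay in the atorvastatin group with poor scores, while their placebo counterparts have died and contribute nothing. Discharge removes the best scores from both arms. A real survival benefit could then appear beside apparently worse organ-failure and severity scores.

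**Working it through.** **Inputs from the documents.** Control 28-day mortality 60%; planned difference 0.2, hence 40% on atorvastatin; 97 per arm raised to 110; 1:1 allocation; alpha 0.05 with a chi-square test. The Sample size section attaches the 0.4 to the non-statin group. Since the same section puts control mortality at 60%, 0.4 is read here as the atorvastatin rate.

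**Inputs not in the documents.** The share of survivors discharged by each day, and how strongly severity predicts death. Both are assumed below and shown over a range.

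**Step 1: the plan's own figure.** The plan says: "A sample size of 97 patients in each group would achieve at least 80 % power". Two-sided test, no continuity correction:

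n = [1.960·√(2·0.5·0.5) + 0.842·√(0.6·0.4 + 0.4·0.6)]² / 0.2² = [1.386 + 0.583]² / 0.04 = 96.9, that is 97.

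This reproduces the stated size (power 80.0%), so 60% versus 40% are the planning rates.

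**Step 2: how many can have a day-28 value.** Number = 110 × survival × (1 − share of survivors discharged), taking the same share in both arms:

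| Survivors discharged by day 28 (assumed) | Placebo | Atorvastatin |
|---|---|---|
| 0% | 110 × 0.4 = 44 | 110 × 0.6 = 66 |
| 50% | 22 | 33 |
| 80% | 8.8, about 9 | 13.2, about 13 |
| 90% | 4.4, about 4 | 6.6, about 7 |

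The first row needs no discharge assumption. Death alone leaves 60% of placebo and 40% of atorvastatin patients without a score, a 20-point imbalance produced by the primary effect.

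**Step 3: direction and size of the bias.** Suppose severity is standard normal, the drug changes survival only, and no patient's score is altered.

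- If severity fully determines death, placebo survivors are the least ill 40% and atorvastatin survivors the least ill 60%. The mean of the lowest fraction f is −φ(z)/f, where z is the f-quantile. Here φ(0.253) = 0.386 for both fractions.
- Placebo: −0.386/0.4 = −0.966. Atorvastatin: −0.386/0.6 = −0.644. Gap: 0.32 SD, with atorvastatin looking worse although no score changed.
- If severity and the risk of death correlate at r, the gap is r × 0.322: about 0.10 SD at r = 0.3, 0.16 at 0.5, 0.23 at 0.7, and 0 at r = 0.
- A simulation of 2,000,000 draws gave the same values. With 10% to 30% of patients also removed by discharge, by the same rule in both arms, the gap at correlations from 0.3 to 1 was about 0.1 to 0.28 SD.

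**Step 4: set against the related outcome.** A patient discharged on day 10 is a success for time to clinical improvement, but has no WHO scale value on days 14 and 28. The plan uses discharge as information in one place and loses it in the other.

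**The case against.** The strongest reply is that the faulted comparison is never stated. The statistical methods name a test for mortality, a logistic model for mortality and a linear model for ventilation duration, but no between-arm test for CRP, SOFA or the WHO scale. The in-hospital sentence can be read as describing data collection only, and the handling of deaths and discharges might sit in an analysis plan that is not shown. The missing-data sentence also does not say that values after death count as missed data.

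This is fair as far as it goes, and the point does not rest on a missing test. It rests on two rules that are stated: a measurement window that ends at death or discharge, and a choice between available data and multiple imputation. Followed as written, they give either a comparison of selected inpatients or values imputed after death.

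Some stronger readings are tempting and not supported:

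- **That the results will reverse.** An example can be built. Assume that at day 14 control is 50% dead, 20% discharged and 30% admitted, with 10% at each of scores 5, 6 and 8, and that atorvastatin is 35%, 25% and 40%, with 8%, 8% and 24% at those scores. Inpatient means are 1.9/0.30 = 6.33 versus 2.8/0.40 = 7.00. Scoring death 10 and discharge 2 gives 5.0 + 0.4 + 1.9 = 7.3 versus 3.5 + 0.5 + 2.8 = 6.8. But the reversal comes from placing 24 of 40 atorvastatin inpatients at score 8, against 10 of 30 controls. With the control mix in both arms, both inpatient means are 6.33.
- **That most patients will be dead or discharged by day 14.** No discharge rate or day-14 mortality is given.
- **That all four days are equally affected.** The effect at day 3 is likely small.
- **That every date needed is already held.** The data collection section {18a} names the discharge date, not the date of death.

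**Conclusion.** The point stands. At later days, chiefly 14 and 28, the stated rules compare groups formed after randomisation, which does not deliver the intention-to-treat analysis announced in {20c}. The ceiling of 44 versus 66 of 110 at day 28 follows from the plan's own mortality rates. Lower counts depend on discharge shares that the document does not give. A spurious disadvantage of about 0.1 to 0.3 SD rests on a normal severity model, a drug that affects survival only, and severity-death correlations from 0.3 to 1; it is zero if severity and death are unrelated. A reversed conclusion is possible but not demonstrated.

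The primary outcome is untouched, because 28-day mortality is ascertained by telephone or the national death index whether or not the patient is in hospital. The matter concerns how the secondary scores can be interpreted and should be settled before they are compared by arm.

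**What to change.** - **WHO scale.** Analyse every randomised patient at each scheduled day. Give deaths the worst category and patients discharged alive a single out-of-hospital category. Compare the arms with a proportional-odds model or a rank test. Use the recorded discharge date and the vital status already ascertained, and confirm that the date of death is captured, since days 3, 7 and 14 need it.
- **Missing data.** State in {20c} that no score is imputed after death, and that multiple imputation is reserved for values that exist but were not recorded.
- **SOFA, CRP and D-dimer.** Report them as descriptive inpatient data, with the numbers dead, discharged and still admitted by arm at each day. For SOFA, a rank analysis with death worst can be added as a sensitivity analysis. Where discharged patients should rank against inpatients with low scores is debatable, so this should not be the main analysis.

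The cost is a change of analysis wording and one check of the case report form, with no new visits. The drawback is that results appear as ranks or odds ratios in place of simple means. As recruitment has ended, the change should be dated and recorded as made before these scores are compared by arm.

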### Participant timeline {13}

We started enrolment on August 17, 2021, and finished recruitment on October 6, 2021. The ascertainment of the primary outcome for the last enrolled patient was on November 2. Figure 1 shows the timeline of the study.

**Fig. 1 Fig1:**
[figure not shown]
Schedule of enrolment, interventions, and assessments according to the SPIRIT template for the study timepoints

### Sample size {14}

A sample size of 97 patients in each group would achieve at least 80 % power to detect a risk difference of 0.2 (20%) in the 28-day all-cause mortality (primary outcome) between the null hypothesis (both proportions are 0.6) and the alternative hypothesis (the proportion in the non-statin group would be 0.4).

Based on two large studies on chronic use of statin in hospitalized COVID patients, the adjusted OR of mortality was 0.52 and 0.67, which corresponds to a risk reduction of 17–27 % in mortality when the mortality is 60% in the control group; therefore, we used the 20% reduction in our assumption of the sample size [21, 22].

We assumed a significance level (*α*) of 0.05 and used the chi-square test of independent proportions in MedCalc software.

To compensate for the estimated loss-to-follow-up, we increased the sample size to be 110 patients in each group.

The mortality in the control group (60%) was estimated from the average mortality in January, February, and March 2021 at the Mansoura University Isolation Hospital among all hospitalized patients.

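### The sample size takes 20% from a relative-reduction range and enters it as an absolute 20-point difference, so the 80% power does not apply to the cited effects

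*Protocol article*

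**What the plan says.** Everything needed is in the protocol article under Sample size {14}.

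- The calculation: with 97 patients per arm the trial is said to have at least 80% power, and the effect is an absolute one: "to detect a risk difference of 0.2 (20%) in the 28-day all-cause mortality (primary outcome"). The null has both proportions at 0.6. Under the alternative, "the proportion in the non-statin group would be 0.4". Alpha is 0.05, the test is the chi-square for independent proportions, and the number is raised to 110 per arm for loss to follow-up.
- The justification: two studies with adjusted odds ratios for mortality of 0.52 and 0.67. These are converted to a 17–27% reduction, and the sentence goes on: "in mortality when the mortality is 60% in the control group; therefore, we used the 20% reduction in our assumption of the sample size".
- Control mortality: 60%, from the hospital's own average for January to March 2021.

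The section does not say whether the 17–27% is relative or absolute.

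**The concern.** The justification and the calculation seem to use the same figure, 20%, on two different scales. If the 17–27% is a relative reduction, a value picked from inside that range cannot be entered as a difference of 0.20 between two proportions when the control rate is 60%. A 20% relative reduction from 60% is 12 points, not 20.

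At stake is what the 80% power refers to. The text invites the reader to take the trial as having 80% power for an effect of the size seen in the cited studies. If that is not so, a non-significant mortality result could be mistaken for a well-powered exclusion of that effect.

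The alternative hypothesis also places the 0.4 rate in the arm without the statin, although the same section puts control mortality at 60%. Read literally, the benefit falls on the wrong arm.

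**Working it through.** **Inputs, all from Sample size {14} unless stated.** Control mortality 0.60; alternative 0.40; alpha 0.05; power 80%; odds ratios 0.52 and 0.67; 97 per arm, raised to 110. Allocation is 1:1 (Methods section). Sidedness is not stated; two-sided is assumed because it reproduces 97.

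**Step 1. Reproduce 97.** Chi-square for two proportions with pooled variance under the null and no continuity correction, where p̄ is the mean of p₁ and p₂:

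n = [1.960·√(2p̄(1−p̄)) + 0.842·√(p₁(1−p₁)+p₂(1−p₂))]² / (p₁−p₂)²

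For 0.60 v 0.40: p̄ = 0.50, the first root is √0.50 = 0.7071 and the second is √0.48 = 0.6928.

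n = (1.3859 + 0.5831)² / 0.04 = 96.9, so 97 per arm. The plan's figure is reproduced, with power 80.0%. The variants tried do not give 97: two-sided with continuity correction 107, one-sided 77, one-sided with correction 86, unpooled two-sided 95.

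**Step 2. Convert the odds ratios.** The control odds are 0.6/0.4 = 1.5, so treated mortality is p = 1.5·OR / (1 + 1.5·OR).

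- OR 0.52: 0.78/1.78 = 43.8%. Absolute reduction 16.2 points; relative reduction 16.2/60 = 27.0%.
- OR 0.67: 1.005/2.005 = 50.1%. Absolute reduction 9.9 points; relative reduction 9.9/60 = 16.5%.

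The relative figures match the stated 17–27%; the absolute ones do not.

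**Step 3. Could 17–27% be absolute?** A 17-point drop gives 43% mortality and OR (0.43/0.57)/1.5 = 0.50. A 27-point drop gives 33% and OR (0.33/0.67)/1.5 = 0.33. Neither pair fits 0.67 and 0.52, so the range can only be relative.

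**Step 4. What was entered.** 60% to 40% is 20 points, a relative reduction of 20/60 = 33%, and OR (0.4/0.6)/1.5 = 0.44. This lies beyond the stronger of the two cited effects.

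**Step 5. Power for the cited effects.** Two-sided alpha 0.05, control 60%, with

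power = Φ{[(p₁−p₂)√n − 1.960·√(2p̄(1−p̄))] / √(p₁(1−p₁)+p₂(1−p₂))}

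| Effect | Treated mortality | Power, 97/arm | Power, 110/arm | n/arm for 80% |
|---|---|---|---|---|
| Entered: 20 points, OR 0.44 | 40.0% | 80.0% | 84.8% | 97 |
| OR 0.52 | 43.8% | 61.8% | 67.3% | 149 |
| 20% relative | 48.0% | 38.8% | 43.0% | 270 |
| OR 0.67 | 50.1% | 28.1% | 31.2% | 398 |

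Solving the same formula for 80% power at 110 per arm gives a difference of 18.8 points.

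**Step 6. Sensitivity to sidedness.** One-sided power at 97 per arm would be 73% for OR 0.52 and 40% for OR 0.67, still below 80%.

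**Step 7. The arm label.** The formula is unchanged if the two proportions are exchanged, so giving 0.4 to the non-statin arm does not alter n. It does contradict the 60% control rate in the same section.

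**The case against.** **No power figure is miscalculated.** The plan claims 80% for 0.6 v 0.4, and 97 per arm delivers it. The section never states 80% power for odds ratios of 0.52 to 0.67. A reader might infer from this point that the power calculation itself is wrong; it is not. This objection stands and limits the point to the step from the cited effects to the input.

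**97 is the less favourable number.** The trial recruited to 110 per arm, and deaths are ascertained by telephone or the national death index, so loss may be small. That is fair, and both columns are shown. No cited effect reaches 80% in either.

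**A 20-point effect has other support.** The background mentions an adjusted hazard ratio of 0.58 for COVID-19 mortality. Assuming proportional hazards over 28 days, treated mortality would be 1 − 0.4^0.58 = 41.2%, a reduction of 18.8 points, with power 75% at 97 and 80% at 110. This shows that an effect near 20 points is not without any basis in the document. The sample size section does not use that figure, however. It derives its 20% from the two odds ratios, and that derivation fails.

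**The cited studies concern chronic users, whom the trial excludes.** A reader might add this as a further contradiction ("Based on two large studies on chronic use of statin in hospitalized COVID patients" against "Exclusion criteria were chronic statin use"). The documents do not support that reading. The plan openly says what the studies are, and extrapolating from existing users to new users is a design judgement that cannot be assessed without the sources.

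**Recruitment is finished.** True, so the sample size cannot be the remedy. The justification will still be read beside the results.

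**Conclusion.** The concern holds as a scale error in the justification. The cited odds ratios support reductions of 9.9 to 16.2 points at 60% control mortality, and the plan entered 20. Power for the cited range is 28–62% at 97 per arm and 31–67% with all 110 analysed; for a 20% relative reduction it is 39% or 43%. The swapped arm label is a separate slip with no effect on the numbers.

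Two stronger conclusions do not follow. The first is that a non-significant result would be presented as evidence against atorvastatin. The documents say nothing of the kind, and they commit to reporting a 95% confidence interval. At OR 0.52 the trial would miss the effect about 38% of the time at 97 per arm (100 − 62), so it would not usually miss it. The second is that the plan needs a fixed margin, such as 10 points, for reading a negative result. The documents define none, and one added after recruitment would be post hoc.

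The figures assume a two-sided test without continuity correction, 60% control mortality as planned, and adjusted odds ratios applied directly to that rate, as the plan itself does.

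**What to change.** Rewrite the sample size section as follows.

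1. State the reductions on both scales: at 60% control mortality, OR 0.52 and 0.67 mean 27% and 16.5% relative, or 16.2 and 9.9 points absolute.
2. State that 80% power applies to a 20-point difference at 97 per arm (33% relative, OR 0.44), or about 19 points at 110 per arm, and that this exceeds both cited effects.
3. Give the power for the cited range at both sizes: 28–62% at 97 per arm and 31–67% at 110.
4. Assign the 0.4 rate to the atorvastatin group.
5. Add that a non-significant primary result will be interpreted through the 95% confidence interval already planned under Statistical methods {20a}, and not as an 80%-powered exclusion of the cited effects.

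The cost is wording only. No patients, tests or analyses change. The price is a less favourable power statement.
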